### Trial monitoring

Monitoring activities will be conducted overall, per site and per hospital. WHO has prepared standard operating procedures for all monitoring activities. In-person monitoring visits to participating hospitals will be conducted by country investigators, WHO staff and external, independent clinical trial monitors. These visits will verify that the trial is being conducted according to the study protocol and manual of operations, including screening and informed consent procedures, storage and use of study intervention (i.e. ampoules remaining for each participant), data collection and management, and handling of any adverse events. The frequency and intensity of monitoring will reflect the rate of recruitment and site performance. In the event that any serious or urgent issues are identified, additional monitoring visits or checks will be implemented. The data management team will review per-hospital and per-site rates of recruitment, adverse events and serious adverse events, and other key progress indicators on a monthly basis.

A Data and Safety Monitoring Board (DSMB) has been appointed. The DSMB is made up of five members, including an independent Chair (maternal and newborn baby health epidemiologist), a statistician, and three technical experts (obstetrics/gynaecology, neonatology, bioethics) familiar with the intervention, maternal and newborn baby health care, and clinical trial methodology, with no important conflicts of interest. The DSMB will convene at least annually to review trial progress, as well as review findings of interim analyses (see below). The rates of preselected specific adverse outcomes of interest to the trial (safety outcomes) will be aggregated across treatment groups and reported to the DSMB on a monthly basis. A DSMB member’s review of unexpected adverse events on an ‘as-needed’ basis may be sought.

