Concerns regarding ACS safety and efficacy in low-resource settings were recently raised by the adverse findings of the Antenatal Corticosteroids Trial (ACT) [26]. ACT was a community-based, cluster-randomized implementation trial conducted in six low- and middle-income countries (Argentina, Guatemala, India, Kenya, Pakistan and Zambia). The trial evaluated a multifaceted intervention designed to increase the use of ACS at all levels of the healthcare system. Trial outcomes included stillbirth, neonatal mortality and suspected maternal infections. Among the less-than-5th-percentile newborn babies (a proxy for preterm births), ACS use did not affect the rate of neonatal deaths before 28 days (relative risk (RR) 0.96, 95% confidence interval (CI) 0.87–1.06, *p* = 0.65). Among all births, the risk of perinatal deaths increased (RR 1.11, 95% CI 1.04–1.19), driven by increases in both the risk of neonatal mortality by 28 days (RR 1.12, 95% CI 1.02–1.22) and of stillbirth (RR 1.11, 95% CI 1.02–1.22). Furthermore, the intervention was associated with increased odds of suspected maternal infection in women with births with less-than-5th-percentile (10% vs 6%, odds ratio (OR) 1.67, 95% CI 1.33–2.09) and women overall (3% vs 2%, OR 1.45, 95% CI 1.33–1.58). The ACT findings have raised concerns that ACS use in peripheral levels of the healthcare system in lower-income countries may confer no benefit and are harmful. However, there is currently no trial evidence to guide clinicians as to whether ACS is efficacious or safe in reasonably equipped hospitals in low-resource countries.

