## Methods

### Aims and objectives

The aim of this trial is to determine whether ACS are safe and efficacious for women and newborn babies in hospitals in resource-limited settings when given to women with live fetuses at risk of imminent preterm birth between 26 weeks 0 days and 33 weeks 6 days gestation for the prevention of neonatal death. The primary objectives are to compare the effect of dexamethasone with placebo on stillbirth, neonatal survival and possible maternal bacterial infections when given to women at risk of imminent preterm birth in participating hospitals.

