### Interim analyses and stopping rules

Three interim analyses are planned, based on potential relative reductions of 40%, 30% and 20% at the three time points, with evidence reaching the 0.001 *p* value as required for recommending early stopping according to the Haybittle-Peto rule (see below). Assuming a baseline outcome rate of 25%, these three interim analyses correspond with intervention group outcome rates of 15%, 17.5% and 20%. Allowing for 10% drop-out, the corresponding sample sizes are 816, 1491 and 3447; it was agreed that target sample sizes of 800, 1500 and 3500 for the three planned interim analyses will be used. These correspond to recruitment of 13%, 25% and 58% of the total sample size. Blinded interim analyses will be reviewed by the DSMB. The unblinded interim analyses will also be available to the DSMB statistician, in the event the DSMB decides to review unblinded interim analysis findings. The DMSB may request additional interim analyses, or reschedule interim analyses as needed.

The Haybittle-Peto stopping rule will be applied on the primary outcomes of neonatal death and any baby death. Using this rule, a two-sided test of hypothesis to assess superiority of one of the groups (intervention or placebo) will be conducted. If the result is significant at α = 0.001, the DSMB will consider recommending stopping the trial for superiority of one of the groups. Any recommendation to stop the trial after the results of an interim analysis will not be guided only by statistical considerations, but also by practical issues (adverse events, ease of treatment administration, unanticipated costs), as well as clinical considerations or external new information. The Trial Coordinating Unit (TCU) will be ultimately responsible for early stopping of the trial upon DSMB recommendations.

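### By-arm review of maternal infection is left to DSMB discretion between interims and after 3500 women, and the monthly report meant to prompt it is pooled across arms

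*Protocol article*

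**What the plan says.** All references are to the protocol article.

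- **Aims and objectives.** Safety is half of the question: "The aim of this trial is to determine whether ACS are safe and efficacious for women and newborn babies". Under Outcomes, possible maternal bacterial infection is the third primary outcome.
- **Background, Antenatal corticosteroids.** The earlier cluster-randomized trial is cited as a reason for this one. Among its findings, "the intervention was associated with increased odds of suspected maternal infection in women with births with less-than-5th-percentile (10% vs 6" per cent, with an odds ratio of 1.67 (95% CI 1.33 to 2.09).
- **Trial monitoring.** The rates of preselected safety outcomes "will be aggregated across treatment groups and reported to the DSMB on a monthly basis". The DSMB meets at least once a year and also reviews the interim analyses. In addition, "A DSMB member’s review of unexpected adverse events on an ‘as-needed’ basis may be sought".
- **Interim analyses and stopping rules.** It was agreed that "target sample sizes of 800, 1500 and 3500 for the three planned interim analyses will be used", and "These correspond to recruitment of 13%, 25% and 58% of the total sample size". "The Haybittle-Peto stopping rule will be applied on the primary outcomes of neonatal death and any baby death", as a two-sided test at 0.001. The DSMB reviews blinded interim analyses. Unblinded results are available to its statistician if the board chooses to see them. The board may ask for more interims or move the planned ones, and adverse events are among the considerations for a stopping recommendation.

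**The concern.** Whether dexamethasone raises maternal infection can be judged only by comparing the arms. The one safety report with a monthly schedule merges them. The planned arm comparisons come at three points, the last at 58% of recruitment, and the only rule stated for them concerns baby deaths. The DSMB can go further, but it needs a reason to, and the regular information it receives cannot tell a drug effect from a high background rate.

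At stake is delay. A large excess of infection could run for months before anyone is prompted to compare the arms, in a trial justified partly by an earlier signal of that kind.

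**Working it through.** **1. The plan's own interim shares.** 800/6018 = 13.3%, 1500/6018 = 24.9% and 3500/6018 = 58.2%. These reproduce the stated 13%, 25% and 58%. What follows the last planned look is 6018 − 3500 = 2518 women, or 41.8%.

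**2. Calendar time.** Trial status gives 24 December 2017 to October 2020. Taking mid-October and a uniform pace (both assumptions), that is 33.7 months, or 6018/33.7 ≈ 179 women a month.
- Second to third interim: 2000/179 ≈ 11 months.
- After the third interim: 2518/179 ≈ 14 months.

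**3. An excess of the size cited.** The background is 10% (Sample size) and the odds ratio 1.67 (Background). Carrying that ratio over to this trial is an assumption.
- Odds on placebo: 0.10/0.90 = 0.1111. Times 1.67 = 0.1856.
- Risk on dexamethasone: 0.1856/1.1856 = 15.7%.
- Pooled rate: (10 + 15.7)/2 ≈ 12.8%.

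A rate of 12.8% in both arms, with no drug effect, gives the same pooled report.

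**4. The same excess seen by arm.** With 10% loss, the number per arm is k = 0.9N/2, which is 675 at N = 1500 and 1575 at N = 3500.

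z = (p₁ − p₀) / √{[p₀(1 − p₀) + p₁(1 − p₁)]/k}

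With p₀ = 0.10 and p₁ = 0.1565, the difference is 0.0565 and the bracket is 0.0900 + 0.1320 = 0.2220.
- N = 1500: 0.0565/√(0.2220/675) = 0.0565/0.01814 ≈ 3.1
- N = 3500: 0.0565/√(0.2220/1575) = 0.0565/0.01187 ≈ 4.8

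**5. Range over other assumptions.**

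| Placebo vs dexamethasone | Pooled rate | z at 1500 | z at 3500 |
|---|---|---|---|
| 10% vs 12.5% (the noninferiority margin) | 11.25% | 1.5 | 2.2 |
| 10% vs 15.7% (odds ratio 1.67) | 12.8% | 3.1 | 4.8 |
| 6% vs 10% (rates in the earlier trial) | 8% | 2.7 | 4.1 |

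In every row the pooled figure is consistent with no difference between arms. These z values assume that every woman counted at a look has complete outcome data, and they ignore stratification by hospital.

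**6. Would a formal infection boundary at 0.001 help?** For 10% vs 12.5%, its power is about 1%, 3% and 14% at 800, 1500 and 3500 women. It would mostly miss an excess the size of the margin, so regular sight of the data by arm matters more than a boundary.

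**The case against.** A reader might infer that harm to mothers cannot be seen by arm between interims, or that the last 2518 women are followed on pooled data only. The article does not support that. The section on interim analyses lets the board review unblinded findings and add or reschedule interims at any time. A two-sided comparison of the arms also implies that the blinded interims keep them apart under code, although the article does not say so. The baby-death rule works in both directions, so the gravest harm reported by the earlier trial is covered at each interim. Limiting the formal rule to mortality fits the Sample size section, which treats the baby outcomes as possibly the weightier ones. All of this stands.

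A reader might also infer that a real excess would look reassuring, because 6% vs 10% pools to 8%, below the planned 10%. That sets one trial's background against another's. On this protocol's own 10% background, the same odds ratio gives 12.8%. With 1350 women contributing data, that is 0.0283/√(0.10 × 0.90/1350) ≈ 3.5 standard errors above plan, if the 10% were known exactly. A rise would be noticed. But the 10% is a planning estimate drawn from earlier trials, so a higher rate has an innocent explanation to hand.

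Report contents may also be settled in a DSMB charter or full protocol that is not shown. That is a fair limit on what can be said about the interim reports, whose outcomes the article does not list. It does not touch the monthly pooling, which the article states outright.

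The other safeguards only partly fill the gap. The as-needed review is for unexpected events, whereas infection is a prespecified outcome. Adverse events are mentioned as a consideration when a stopping recommendation follows an interim, and none is planned after 3500.

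**Conclusion.** The point holds as a minor one. By-arm review of maternal infection is discretionary, not absent: nothing schedules it for about 11 months between the second and third interims, or for the last 41.8% of recruitment (about 14 months). The routine prompt for using that discretion is a pooled rate that cannot assign an excess to an arm. An excess as large as the one cited would give z of about 3.1 at 1500 women and 4.8 at 3500 if shown by arm.

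The durations rest on uniform recruitment to mid-October 2020. The z values rest on 10% loss, a 10% background and an odds ratio carried over from a different setting. The case for a formal infection boundary is not made: its power for a margin-sized excess is low.

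**What to change.** - **Trial monitoring.** Give the DSMB the preselected safety outcomes by coded arm, with the key held by its statistician, and name possible maternal bacterial infection among them. Keep pooled tables for the coordinating unit and the sites.
- **Interim analyses and stopping rules.** State that maternal infection is tabulated by coded arm at each interim and at one further scheduled safety review between 3500 and 6018 women, for the board's judgement and without a new formal stopping boundary.

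The cost is wording in the protocol, DSMB charter and report template, plus minor extra programming. The small downside is that the board sees coded-arm data more often. The tests and significance levels for the baby-death outcomes do not change.

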### Interim analyses and stopping rules

Three interim analyses are planned, based on potential relative reductions of 40%, 30% and 20% at the three time points, with evidence reaching the 0.001 *p* value as required for recommending early stopping according to the Haybittle-Peto rule (see below). Assuming a baseline outcome rate of 25%, these three interim analyses correspond with intervention group outcome rates of 15%, 17.5% and 20%. Allowing for 10% drop-out, the corresponding sample sizes are 816, 1491 and 3447; it was agreed that target sample sizes of 800, 1500 and 3500 for the three planned interim analyses will be used. These correspond to recruitment of 13%, 25% and 58% of the total sample size. Blinded interim analyses will be reviewed by the DSMB. The unblinded interim analyses will also be available to the DSMB statistician, in the event the DSMB decides to review unblinded interim analysis findings. The DMSB may request additional interim analyses, or reschedule interim analyses as needed.

The Haybittle-Peto stopping rule will be applied on the primary outcomes of neonatal death and any baby death. Using this rule, a two-sided test of hypothesis to assess superiority of one of the groups (intervention or placebo) will be conducted. If the result is significant at α = 0.001, the DSMB will consider recommending stopping the trial for superiority of one of the groups. Any recommendation to stop the trial after the results of an interim analysis will not be guided only by statistical considerations, but also by practical issues (adverse events, ease of treatment administration, unanticipated costs), as well as clinical considerations or external new information. The Trial Coordinating Unit (TCU) will be ultimately responsible for early stopping of the trial upon DSMB recommendations.

### Training

Prior to commencement of recruitment, study site research teams complete an in-person training workshop on study procedures, according to a standardized study manual of operations. This workshop emphasizes GCP standards, the need for accurate and thorough data reporting and vigilance in identifying, detecting and reporting any possible adverse events, safety concerns or protocol deviations. Country and hospital investigators will maintain a valid GCP certificate throughout the trial. Standardized training for relevant staff will also be conducted at study sites to optimize use of obstetric ultrasound for gestational age estimation, use of transcranial ultrasound for assessment of neonatal intraventricular haemorrhage, and essential care of preterm newborn babies.

### Trial oversight

The TCU comprises staff from two WHO departments (maternal and newborn babies) and the trial statistician. The principal investigators are experienced maternal and neonatal health researchers from participating sites. The trial steering group (TSG) is composed of the TCU, the principal investigators, a group of external technical advisors and an independent Chair. Members of the TSG do not have important conflicts of interest. Any major changes to the study protocol will be decided by the TSG, and communicated to the relevant ethical committees and trial registry.

### Ethical considerations

The trial protocol was reviewed and approved by the WHO Ethics Review Committee (ERC.0002851). All participating sites received ethics approval from the relevant IRBs (see Additional file 4), as well as the relevant national regulatory authorities. Annual reports on study progress will be provided to these committees. Informed consent will be obtained from all study participants prior to their participation by study staff. An international clinical trial insurance provider has been engaged to provide indemnity insurance for trial participants.

## Discussion

Preterm birth is an important global public health issue, affecting an estimated 15 million live births worldwide each year [1]. The safety and efficacy concerns surrounding use of ACS in hospitals in low- and middle-income countries have arrested efforts to scale-up the use of ACS in these settings.

This trial will address key knowledge gaps around efficacy and safety of ACS in low-resource countries, and strengthen the overall evidence base on the efficacy of ACS by doubling the number of participants in the Cochrane review on this topic [23].

This trial has several strengths. It will recruit participants across five low-resource countries in sub-Saharan Africa and south Asia and is powered for critical mortality outcomes of the baby and possible effects on infectious morbidity in women. No previous trial has been independently powered for neonatal mortality, and trials have generally not followed participants into the community to assess impacts on neonatal mortality to 28 days of life. The ACTION-I trial will use standard definitions of maternal and newborn baby outcomes to 28 completed days after birth, and standard collection procedures to measure these outcomes. The eligibility criteria are not overly selective, ensuring that results will generalize to women at risk of imminent preterm birth. The hospitals have been carefully selected to reflect the minimum requirements for maternal care of women at risk of imminent preterm birth, as well as adequate care of preterm newborn babies. It is thus anticipated that the findings will be generalizable to other, similar hospitals in low- to middle-income countries.

Results of this trial will be published in a peer-reviewed, open-access journal by the WHO ACTION Trials Collaboration. The trial will also inform the update of the evidence base supporting WHO recommendations on ACS use, national and local clinical guidelines, and policies on ACS use. Currently corticosteroids are widely available, and dexamethasone sodium phosphate (4 mg/mL) is already listed on the WHO Model Essential Medicines List for use in preterm birth [28]. Hence, we anticipate that if this trial demonstrates efficacy, access to ACS should not face the challenges of a new drug or formulation.

## Trial status

Version 1.10 (6 February 2018) commenced recruiting 24 December 2017. The expected date to complete recruitment is October 2020.

## Data Availability

Not available.

## Abbreviations

ACS: Antenatal corticosteroids
ACT: Antenatal Corticosteroids Trial
ACTION: Antenatal Corticosteroids for Improving Outcomes in preterm Newborns
DSMB: Data and Safety Monitoring Board
GCP: Good clinical practice
IQR: Interquartile range
IRB: Institutional Review Board
ITT: Intention-to-treat
PP: Per-protocol
SMS: Short message service
SPIRIT: Standard Protocol Items: Recommendations for Interventional Trials
TCU: Trial Coordinating Unit
TSG: Trial Steering Group
WHO: World Health Organization
